### Qualitative data analysis

With regard to the qualitative study among therapists and patients, we plan to employ a thematic analytic approach, combining both a top-down approach with pre-formulated themes and a bottom-up approach that allows new themes to emerge from the interviews (64). Inter-rater agreement will be assessed using blinded double coding. Rather than aiming for statistical representativeness, our sample prioritizes diversity. Participants will be selected based on a range of factors: treatment site, sex, age, ethnic background, treatment outcomes (success or failure), and treatment completion or premature termination (65).

### Data management, storage, monitoring, and dissemination

Data are collected using a web-based tool called Lotus, developed by the University of Amsterdam. The tool is used to monitor the progress of patients and remind research assistants and junior researchers of upcoming assessments. The patients are registered in Lotus and assigned a unique identifier to maintain their anonymity. The personal information of patients is stored in a secure location and is accessible only to authorized personnel. The data are collected through a secure online survey software called Qualtrics (66) and stored on a secure server accessible only to authorized researchers. The Study Board, consisting of the steering committee, shares ownership of the data and makes the final decisions. The data will not be publicly available because of their sensitive nature. The results of this study will be disseminated through publications in scientific journals and presentations at conferences. Training and supervision will also be offered to participating clinicians to facilitate implementation. The site coordination committee is responsible for addressing the potential difficulties in the execution of the study.

### Safety

Previous studies (see Background Section) suggest that there is no significant risk for patients undergoing the treatments being investigated. To minimize any potential harm, patients with acute suicidality are excluded from the study. In cases of serious adverse events (SAEs), which include events resulting in death, hospitalization, or significant disability, the junior researcher will be notified within 24 h by the local site coordinators. The relatedness of the SAE to the intervention will be evaluated by the PIs and reported to the ethical committee of the University of Amsterdam. Because the occurrence of SAEs is expected to be low, no specific hypotheses were formulated with regard to conditions and SAEs. However, the number and type of SAEs will be reported per study arm in the outcome paper.

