## Method

### Design

This study design is a multicenter RCT, with two arms (*n* ≥ 73). Both treatments consist of a combination of individual and group sessions. There are two versions of individual ST, to which participants are randomly assigned: (A) experimental ST, in which ImRs is delivered in every individual session during months 2–4 (early ImRs), and (B) STAU, in which patients receive ST-as-Usual, that is, ImRs is not allowed during months 2–4. Therapists in this condition are allowed to use other ST (experiential) techniques, such as chair work and cognitive and behavioral techniques, but are not allowed to use ImRs. After 4 months, therapists are free to use all ST techniques that they think are appropriate and helpful. This study is being carried out in five corporate mental healthcare centers in the Netherlands: GGZ Oost Brabant (locations Helmond and Oss), and PsyQ locations Amsterdam, Rotterdam, and Zaandam. During the study, the PsyQ location in Amsterdam was taken over by the Academic Center for Trauma and Personality (ACTP).

In two PsyQ sites (Amsterdam and Rotterdam), several participants also took part in the Borderline Optimal Treatment Selection (BOOTS) study. The BOOTS study compares the effectiveness of DBT to ST and investigates the optimal treatment selection among individuals with BPD (21). Eighteen participants participated in the BOOTS trial and were randomized to the ST arm. They completed the assessments needed for the BOOTS and the LUCY trial, after which they were randomized to one of the two arms of the LUCY trial.

The study protocol was approved by the ethical committee of the University of Amsterdam (2019-CP-10845). This study is registered at the International Clinical Trial Registry Platform, registration number NL NL7965, first registered on 15 August 2019 and fulfills the World Health Organization Trial Registration Data Set. The procedures adhered to applicable guidelines and regulations. Any changes in the protocol will undergo formal amendments. The ethical committee of the University of Amsterdam will review the amendments, and, upon approval, they will be included in the trial registration.

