#### Escape medication/treatment

If the participants experience an acute crisis during the study, they are permitted to use other forms of therapy or medication. The use of such interventions or medication will not result in exclusion from the study but will be recorded, monitored, and reported.

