#### Primary outcome measures

The primary focus of the study is to determine changes in the severity and frequency of DSM-5 BPD manifestations, assessed with the Borderline Personality Disorder Severity Index version 5 (BPDSI-5) (42). The BPDSI-5 is a structured clinical interview that employs 70 items to assess the severity of BPD within the preceding 3 months. The items assess different manifestations of the nine BPD traits outlined in the DSM-5. Each of these nine traits is evaluated using multiple items. The frequency of occurrence indicated by each item is evaluated using an 11-point Likert scale, ranging from 0 (absent) to 10 (daily). However, the 'identity disturbance' trait diverges, utilizing a 5-point Likert scale from 0 (not present) to 4 (dominant), which is then multiplied by 2.5. For each BPD trait, a subscale score is calculated consisting of the mean of the pertinent items (range 0–10). The total score of the BPDSI-5 score ranges from 0 to 90, reflecting overall severity. The psychometric properties of the BPDSI-5 are good, with a high level of agreement between different raters and high internal consistency. The scale has a cutoff point of 14.93 with scores above, indicating clinical levels of BPD dysfunction and exhibiting considerable specificity (1.00) and sensitivity (0.97). Additionally, Giesen-Bloo et al. (42) concluded that a reliable positive change is indicated by an improvement of at least 11.70 points.

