Fourth, the study tests the hypothesis that early application of ImRs leads to reduced treatment retention, a prediction that follows from the original ST protocol. In other words, the focus is not only on possible positive outcomes but also on the possible negative effects of early trauma processing.

Fifth, the focus is not on the treatment of PTSD in participants with a double diagnosis of BPD and PTSD but on treating any kind of negative early childhood experiences that contributed to the development of BPD. The conceptualization of this study and the hypotheses being investigated are based on an acknowledgment of the importance of such adverse events in the etiology of personality pathology and in the treatment of BPD. This is important because sadly, many adverse childhood experiences are often neglected even when there is a diagnosis of PTSD (69).

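### The SAE summary per arm names no reporting period or person-time, so an early excess could be hard to see if only whole-study counts are shown

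*Protocol article*

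**What the plan says.** The Safety section commits to one output for the results paper: "the number and type of SAEs will be reported per study arm in the outcome paper". It explains why nothing more formal is planned: "Because the occurrence of SAEs is expected to be low, no specific hypotheses were formulated with regard to conditions and SAEs". It adds that "The relatedness of the SAE to the intervention will be evaluated by the PIs", with a report to the ethics committee. Site coordinators notify the research team of SAEs within 24 hours.

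The Design and Treatment sections set the contrast between arms. Month 1 is introductory in both. In months 2–4, arm A uses ImRs in each individual session and STAU may not use it. From then on the restriction ends: "After 4 months, therapists are free to use all ST techniques that they think are appropriate and helpful". The Abstract gives a maximum treatment duration of 25 months, and Table 1 has a last assessment at month 36.

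Other treatment or medication used in an acute crisis "will be recorded, monitored, and reported" (Escape medication/treatment). Medication and mental healthcare use are monitored at every assessment (Secondary outcome measures, item 10).

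**The concern.** The trial asks about timing. The Introduction gives patients' possible unreadiness as a reason for postponing trauma processing, so if early ImRs causes acute harm, months 2–4 are a natural place to look. The Safety section names arm, number and type, and leaves out when an event occurred and how long patients were observed.

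Two things are at stake. First, a count over the whole study adds many months in which the arms are not required to differ. A cluster of early events in arm A could then look like near-equality. Second, a count without patient-months is hard to read if the arms lose patients at different rates. The Sample size section itself considers first-year dropout of 20% against 50%. If patients who leave treatment are also observed less completely for SAEs, the arm with more dropout could look safer than it is.

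**Working it through.** **The plan's own figure.** The Safety section gives no SAE rate, expected count or power, so there is nothing to reproduce. The event rates and rate ratios below are assumptions.

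**Inputs from the protocol article**
- Months in which the arms differ by rule: 3 (months 2–4).
- Maximum treatment duration: 25 months; last assessment: month 36.
- N = 73 at 1:1, taken as 36 per arm.

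**Share of time.** 3/25 = 12.0% of treatment and 3/36 = 8.3% of the study. The 36 months divide into month 1 (no ImRs in either arm), months 2–4 (the contrast), months 5–25 (21 months, ImRs open to both) and the remaining 11 months, mostly the follow-up year, which is intended to be treatment-free.

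**Effect on the ratio.** Assume a constant event rate and complete follow-up, with the rate multiplied by R in arm A in months 2–4 only. Over T months the ratio is (T − 3 + 3R)/T.

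| R in months 2–4 | 25 months | 36 months |
|---|---|---|
| 2 | (22 + 6)/25 = 1.12 | (33 + 6)/36 = 1.08 |
| 3 | (22 + 9)/25 = 1.24 | (33 + 9)/36 = 1.17 |
| 4 | (22 + 12)/25 = 1.36 | (33 + 12)/36 = 1.25 |

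**Effect on the counts.** Assume 0.2 SAEs per patient-year and R = 3. The expected count in arm B is 36 × T × 0.2/12. Arm A adds 36 × 3 × (0.2/12) × 2 = 3.6 events.

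| Period | A | B | Difference | Difference / √(A + B) |
|---|---|---|---|---|
| Months 2–4 | 5.4 | 1.8 | 3.6 | 3.6/√7.2 = 1.3 |
| 25 months | 18.6 | 15.0 | 3.6 | 3.6/√33.6 = 0.6 |
| 36 months | 25.2 | 21.6 | 3.6 | 3.6/√46.8 = 0.5 |

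The absolute excess is 3.6 events in every row. The ratio falls, and so does the excess relative to chance variation.

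**What the early window can show.** These are powers of an exact conditional two-sided Poisson test at 0.05, with 36 patients per arm and R = 3.

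| SAEs per patient-year | Months 2–4 | 24 months | 36 months |
|---|---|---|---|
| 0.1 | 3% | 4% | 4% |
| 0.2 | 14% | 7% | 6% |
| 0.4 | 39% | 12% | 10% |

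At 0.2 or 0.4 the early window is the more informative view, yet still weak. At 0.1 no view has useful power. A table by period is therefore description, and a test on it would add little.

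**The case against.** The strongest reply is that the article does not restrict SAE reporting to totals. The word only is absent, no breakdown by period is excluded, and a condensed article commonly leaves tabulation windows to the full protocol or analysis plan, which are not shown. That stands: a reader might infer that whole-study totals are all that will appear, but the text does not say so.

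Other parts of the reply also stand:
- **Contradiction with the Discussion.** A reader might set the Safety section against the stated focus on "the possible negative effects of early trauma processing". That phrase restates the preceding sentence, which concerns treatment retention, and dropout is to be analysed by survival analysis.
- **A false claim of equal safety.** No SAE test or equivalence claim is planned, so predicting that the paper will make one goes beyond the document.
- **Months 2–4 as the main safety comparison.** The trial compares early ImRs with standard schema therapy. Harm when STAU patients start ImRs later, and delayed harm in arm A, belong to that question. The whole-study count is a valid answer to it.
- **Crisis care without timing.** Monitoring at each assessment already places medication and care use in intervals.
- **Early worsening goes unseen.** The primary interview is designed "to assess the severity of BPD within the preceding 3 months" and is given at month 4, so it already covers the early window. The 11.70-point reliable change is stated for improvement only and is not an established threshold for deterioration.

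The relatedness judgement does not fill the gap. It goes to the ethics committee, whereas the paper is promised number and type. Relatedness to the intervention also need not separate early from later ImRs.

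**Conclusion.** The point holds as a worthwhile improvement to a stated summary. The Safety section names neither a reporting period nor time at risk, while the prescribed contrast covers 3 of up to 36 months. If only whole-study counts were shown, a ratio of 3 in months 2–4 would appear as about 1.24 over 25 months or 1.17 over 36 months.

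This rests on an assumed constant background rate, complete follow-up and excess risk confined to months 2–4. The document gives no SAE rate. If harm were delayed, or followed from more ImRs overall in arm A, the later periods would matter as much, and so the whole-study count must stay. The absolute excess is unchanged by pooling; what weakens is the ratio and its visibility against chance.

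**What to change.** In the Safety section, keep the number and type of SAEs per arm over the whole study. Add that they will also be tabulated descriptively per arm by period: month 1, months 2–4, later treatment and follow-up. Give the patients and patient-months at risk for each arm and period, and say how time after leaving treatment or the study is counted. Show crisis interventions and escape medication in the same way. If these are recorded only by assessment, months 1–4 can be one period; little is lost, because neither arm receives ImRs in month 1.

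Do not name months 2–4 as the main safety comparison, and do not present 11.70 points as an established deterioration threshold. Fix the periods before counts by arm are seen, so that the window cannot be chosen after the fact.

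The cost is one or two sentences and one table, with no new assessments provided that event dates are kept, as 24-hour notification suggests is feasible. The drawback is small counts in each period, so the table can describe but not test.

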### Sample size

At least *N* = 73 participants were planned to be included. Using the approximation proposed by Twisk (25), and assuming an average correlation of 0.5 between measurements [as in (26)], this suffices, given the seven repeated measurements, to reach 80% power to detect a medium effect size of *d* = 0.5 between the treatment conditions. Using the more sophisticated power analysis approach proposed by Moerbeek et al. [(27), p. 191] for multilevel tests of a difference in linear slopes assessed with multiple (i.e., 7) measurements, for a medium effect size (*d* = 0.5) tested at a two-tailed significance level of 0.05, *N* = 39 suffices to reach 80% power. Starting with *N* = 73 and taking into account an early study dropout of 10%, the resulting N=66 suffices to reach > 95% power to detect a medium effect size (*d* = 0.5) and 80% power to detect a small-to-medium effect size of *d* = 0.38. An effect size of *d* = 0.5 between slopes is equivalent to a mean difference between conditions of approximately five points on the BPDSI at the last assessment, which is a relevant difference. Moreover, the sample size of N = 73 suffices to reach more than 80% power to detect at a significance level of 0.05, a difference of 30% in dropout rates during the first year between 20% [which is the approximate dropout rate of ST in individual-group format at 1 year; (26)] and 50%, which would be a substantial and alarming increase in the experimental treatment (25, 28).

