### Randomization

When participants were eligible for participation and completed baseline assessments, they were randomized to one of the two arms A (early ImRs) or B (STAU) in a 1:1 proportion by an independent researcher, after checking the inclusion and exclusion criteria, using block randomization with randomized block sizes blocks (sizes 4 and 6), stratified by the center (for the Amsterdam site stratified for language) (29, 30). The allocated treatment condition was disclosed to the patient by their therapist during the first treatment session.

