### Procedure and assessments

Patients were recruited from participating mental healthcare centers. Patients with a primary diagnosis of BPD, classified using the Structured Clinical Interview for Personality Disorders (SCID-5-PD) (22) by trained clinicians, were asked to participate in the screening process of the study. A check was performed to determine eligibility. This check concerned examining whether participants met the inclusion and exclusion criteria, and their willingness and ability to participate in 2-year individual and group schema therapy.

After the first eligibility check but before randomization, the baseline measurements (see Measures Section) and a motivational/availability interview assessing the participants' motivation were performed by an independent research assistant. After 4, 8, 12, 18, 24, and 36 months, assessments by an independent trained local research assistant blinded to the treatment arm were performed (Table 1). Each assessment took approximately 2.5 h. The results of the assessments were shared with the patients and therapists so that they could be used as routine outcome measures to track and discuss treatment progress. Participants who drop out of treatment and or the study will be asked to continue the study assessments; however, if the participant decides to withdraw from the study, a minimized exit assessment is conducted—if the participant consents, in which the primary outcome measure is assessed. Patients will receive a monetary incentive of 25 euros after completion of all assessments. All group ST sessions are video-recorded, and individual ST sessions are audio-recorded. A random sample will be selected from each site. Independent raters will evaluate a random selection of these recordings to evaluate treatment adherence and competence of group ST with the Group Schema Therapy Treatment Integrity scale (31) and individual ST with Schema Therapist Competency Scale [STCS-I-1; (32)]. The recordings will be destroyed 5 years after the primary study results have been published. The results of the baseline assessments were provided to the therapists to formulate the ST case conceptualization.

**Table 1 T1:** Overview of measures and assessment times.

**Instrument**	**Baseline**	**After 3 sessions**	**4 months**	**8 months**	**12 months**	**18 months**	**24 months**	**36 months**
CTQ-SF	•							
BPDSI	•		•	•	•	•	•	•
WHODAS 2.0	•		•	•	•	•	•	•
WAI-SR		•	•	•	•	•	•	•
BSI	•		•	•	•	•	•	•
PCL-5	•		•	•	•	•	•	•

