8. General psychopathological symptoms as an index of the severity of syndromal disorders are assessed with the Brief Symptom Inventory [BSI; (58)], a short version of the Symptom-Check-List (SCL-90-R). The BSI is a self-reporting instrument that measures general psychiatric symptoms. It measures nine symptom dimensions: somatization, obsession-compulsion, interpersonal sensitivity, depression, anxiety, hostility, phobic anxiety, paranoid ideation, and psychoticism with 53 items scored on a 5-point Likert scale, ranging from 0 (not at all) to 4 (extremely). The BSI has good reliability and validity. The internal consistency of the total score is 0.96, and the test–retest reliability is 0.90 (59). Normative data are available for both clinical and non-clinical samples of adolescents (over 13 years) and adults (60).

9. Happiness is assessed with the 1-item happiness question validated in more than 30 countries (61). General happiness, in the weeks prior to the assessment, is assessed by a single 7-point Likert scale item ranging from 1 (completely unhappy) to 7 (completely happy). The reliability and validity of the happiness item are good to excellent, with a test–retest reliability of 0.87 (62).

10. Medication and mental healthcare use are monitored during each assessment.

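### SAE counts per arm are not tied to follow-up after dropout: no SAE check is linked to the continued assessments, and no observation time is reported beside the counts

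*Protocol article*

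**What the plan says.** The Safety section of the protocol article fixes two things about SAEs, which it defines to include death, hospitalisation and significant disability.

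- **Route:** "the junior researcher will be notified within 24 h by the local site coordinators".
- **Summary:** "the number and type of SAEs will be reported per study arm in the outcome paper". The events are expected to be few, and "no specific hypotheses were formulated with regard to conditions and SAEs".

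Other sections bear on how long a patient stays visible to the study.

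- **Procedure and assessments:** people who drop out of treatment or the study are asked to continue the assessments at 4, 8, 12, 18, 24 and 36 months. Those who withdraw from the study altogether get a reduced exit assessment, "if the participant consents, in which the primary outcome measure is assessed".
- **Secondary outcome measures, item 10:** "Medication and mental healthcare use are monitored during each assessment".
- **Dropout, deviation from the treatment protocol, and follow-up:** site coordinators find alternative care for patients who drop out or are removed from treatment.
- **This study:** early imagery rescripting (ImRs) might raise dropout, but might also lower it.
- **Sample size:** the dropout comparison sets 20% in the first year against "50%, which would be a substantial and alarming increase in the experimental treatment".

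**The concern.** A raw number of events per arm is a fair comparison only if both arms are watched for about the same time and with the same completeness. The one stated SAE route runs through the treating sites, and a coordinator is more likely to hear of an admission while the patient is still in treatment there. The sources that could show later events, namely the continued assessments and the healthcare-use item, are not said to feed the SAE record.

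The trial is expressly interested in whether early ImRs changes retention. If it does, and if capture falls after dropout, the arm that loses more patients would show fewer SAEs than it had. A patient who leaves because treatment went badly could be the one whose later admission is missed. The SAE comparison is descriptive, but readers will use it to judge the tolerability of early trauma processing.

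**Working it through.** **1. The protocol's own figure.** No SAE figure is stated. The figure that can be checked is the dropout scenario: more than 80% power for 20% versus 50% in year 1 with N = 73 at alpha 0.05. I take 1:1 allocation (36.5 per arm) and a two-sided test; the article does not state sidedness for this comparison.

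- Hazard ratio = ln(0.5)/ln(0.8) = 3.11.
- Expected dropouts = 36.5 × (0.2 + 0.5) = 25.6.
- Log-rank power (Schoenfeld) = Φ(√(25.55/4) × ln 3.106 − 1.96) = Φ(0.905) = 81.7%.
- Unpooled z-test: 0.3/√[(0.16 + 0.25)/36.5] − 1.96 = 0.871, power 80.8%.

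The figure reproduces in these forms (a two-sided pooled z-test gives 77.8%), so the scenario is usable as the protocol's own.

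**2. Time in treatment under that scenario.** Assume a constant dropout hazard h, so mean time in treatment up to month T is (1 − e^(−hT))/h.

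- Early ImRs: h = −ln(0.5)/12 = 0.0578 per month.
- Schema therapy as usual (STAU): h = −ln(0.8)/12 = 0.0186 per month.

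| Horizon T | Early ImRs (months) | STAU (months) | Ratio |
|---|---|---|---|
| 4 months | 3.57 | 3.85 | 0.93 |
| 12 months | 8.66 | 10.76 | 0.80 |
| 25 months (maximum treatment) | 13.23 | 19.99 | 0.66 |
| 36 months | 15.15 | 26.24 | 0.58 |

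These are ratios of *observed* time only if SAE capture stops at treatment dropout. The rows beyond 12 months also carry the first-year hazard forward; at 25 months that implies 1 − e^(−0.0578 × 25) = 76% dropout under early ImRs. If dropout is confined to year 1, the ratio is 0.72 at 24 months and 0.69 at 36 months. With 40% instead of 50% first-year dropout under early ImRs, the 25-month ratio is 0.77.

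**3. Allowing for observation after dropout.** Let f be the share of post-dropout time in which an SAE would still be captured. The documents do not give f. Writing m for mean time in treatment in each arm, observed time is m + f(T − m). At T = 25 and f = 0.5:

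- Early ImRs: 13.23 + 0.5 × 11.77 = 19.12.
- STAU: 19.99 + 0.5 × 5.01 = 22.50.
- Ratio: 0.85.

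| f | Ratio, over horizons of 12 to 36 months |
|---|---|
| 0 | 0.58 to 0.80 (0.66 at 25 months) |
| 0.5 | 0.82 to 0.91 |
| 0.75 | 0.92 to 0.96 |
| 0.9 | 0.97 to 0.98 |
| 1 | 1.00 |

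**4. Reading the ratio.** With equal true SAE rates on and off treatment, the ratio of expected raw counts equals the ratio of observed time. At 0.66 the early-ImRs arm would show about 34% fewer events, and a true rate 1/0.66 = 1.5 times higher would look equal. At f = 1 nothing is distorted. With equal dropout, the arms are under-counted alike. If early ImRs lowers dropout, the direction reverses.

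**The case against.** The strongest reply is that the dropout in question is dropout from treatment, and the article does not let observation end there. Dropouts are asked to continue assessments to month 36 with local research assistants. Mental healthcare use is recorded each time, coordinators stay involved when a patient drops out, leavers keep a right to alternative treatment at the centre, and crisis treatment is recorded and reported. The 50% is a power scenario, not a forecast. The assumed 10% early study dropout is not split by arm. The treatment-free follow-up year applies to both arms. Over the first 4 months, which include the months when the arms differ by design, even zero capture after dropout gives 0.93. A condensed article may also leave the SAE window and denominators to the full protocol.

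Most of this stands. A reader might infer that SAEs cease to be observed at treatment dropout, or that the early-ImRs arm will look safer than it is. The documents support neither: the first conflicts with the request to continue assessments, and the second ignores the stated possibility of lower dropout. Nor does the absence of an SAE row in the table of measures prove that nothing is asked, since that table also omits the healthcare-use item collected at every visit.

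What survives is narrower. The article chose to state both the route and the summary, and it links neither the continued assessments nor the healthcare-use item to the SAE record. That item concerns mental healthcare, so it could miss a non-psychiatric admission, and the exit assessment is described only in terms of the primary outcome. Completeness after dropout is therefore not assured by anything written.

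**Conclusion.** The point holds in conditional form. As written, the SAE comparison is a raw count fed by one stated route, with no stated link to the data that would reveal events after dropout. If capture after dropout is incomplete and dropout differs by arm, the count may favour the arm with more dropout, whichever that is.

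At 20% versus 50% first-year dropout, the observed-time ratio runs from 1.00 (full capture) through 0.82 to 0.91 (half captured) to about 0.66 over 25 months (none). The last figure is a worst case that the continued assessments make unlikely to be reached in full. The results rest on a constant dropout hazard, equal SAE rates on and off treatment, and a capture share the documents do not give. A distortion is possible but not established. The remedy is cheap enough to be worth making regardless.

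**What to change.** In the Safety section:

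1. State that SAEs are counted in all randomised patients from randomisation to month 36, whatever their treatment status.
2. State that the SAE record will be reconciled, in the same way in both arms, against the medication and mental healthcare-use data already collected at each assessment.
3. Report, per arm, the patients with at least one SAE and the observation time (or events per person-time) beside the number and type.

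The cost is an amendment, a re-read of records already held, and a few extra figures in the outcome paper. Recalled dates will be imprecise, and mental healthcare records will cover non-psychiatric admissions incompletely. A short SAE question at assessments, including the exit assessment, is optional. The last patient started in January 2023 and the last assessment is planned for January 2026, so it would help only for visits still to come.
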